#### 5.5 Supportive Care

Any antiemetic regimen can be used at the discretion of the investigator.

Rev. 9/97

5.51 Mucositis has been a common toxicity in patients receiving 5-day courses of 5-FU and Leucovorin. Preliminary reports suggest that oral cryotherapy may decrease this toxicity (24). Patients who are assigned to this arm may be offered this therapy; if performed, flow sheets should clearly indicate the patient was so treated.

**Method:** 5 minutes prior to each dose of 5-FU and Leucovorin patients will place ice chips in their mouths and will swish the ice continuously around their oral cavities for 30 minutes, replenishing the ice chips as needed. Patients with dentures should remove them prior to treatment.

Rev. 9/97

## 5.52 Supportive Care Options During Therapy with 5-FU + Leucovorin

Rev. 9/97

Diarrhea has been a common toxicity with 5-FU + Leucovorin therapy, frequently requiring parenteral hydration and significant dose delays and modifications. Preliminary reports suggest that somatostatin analogue (Sandostatin) may more rapidly and completely control diarrhea, which may lead to better protocol compliance and safety (25).

Rev. 9/97, 8/99

Method: In patients with  $\geq$  Grade 1 diarrhea, chemotherapy should be modified as appropriate by protocol. In addition, patients who have  $\geq$  Grade 2 diarrhea should be considered for Sandostatin therapy, 50-100 ug SQ every 8 hours for up to 3 days. When utilized, Sandostatin therapy and response should be recorded on flow sheets.

ECOG investigators may wish to consider entering patients with at least Grade 2 chemotherapy-related diarrhea on E1295, *Randomized Trial of High-Dose Versus Conventional Dose Octreotide Acetate Versus Loperamide In The Treatment of Chemotherapy-Related Diarrhea In Patients With Colorectal Cancer*.

Appropriate dose modifications should continue to be implemented in subsequent treatments, based on the highest grade of diarrhea experienced.

## 5.6 Duration of Therapy

### 5.61 Perioperative 5-FU

Upon receipt of the final surgical pathology report from the contributing institution's pathology department, Dukes' A, B1, and D patient should have perioperative 5-FU chemotherapy **discontinued**. These patients will be removed from the study, and survival data will be collected on them until death. Dukes' B2, B3, and C patients should have perioperative 5-FU **continued** to completion.

### 5.62 Adjuvant 5-FU + Leucovorin

Rev. 9/97

Patients receiving adjuvant 5-FU/leucovorin continue the therapy for a total of 6 months or until recurrence. Once a patient has recurred according to the criteria in Section 6.1, he/she is considered off study and will be followed for survival.

## 6.0 MEASUREMENT OF EFFECT

**Note:** Biopsy confirmation of disease recurrence should be obtained whenever possible with acceptable risk.

### 6.1 Criteria for Disease Progression

6.11 Local recurrence of malignant disease proven by biopsy.

6.12 Positive liver scan, CT, or MRI. This observation should be confirmed by repeat determinations, 1 month apart.

6.13 Pulmonary metastasis by chest x-ray or CT scan.

- 6.14 Bony metastasis by routine x-ray, if previous x-ray of suspected lesion was normal at onset of study. Abnormal bone scans have to be confirmed by routine x-ray and/or biopsy.
- 6.15 A persistent rise in CEA titer of 10 times upper normal value, confirmed on 2 separate determinations at 1 month intervals, in patients who had an initially normal CEA value upon entry into the study. The determination should be performed by the same laboratory, using the same method. The method used should be specified on the Serum Marker Form. Every effort should be made to document the tumor recurrence, including exploratory laparotomy if necessary.
- 6.16 Ascites or pleural effusion with positive cytology for malignant cells.
- 6.17 Anastomotic recurrence, proven by biopsy.
- 6.18 Intraabdominal, abdominal wall or incisional recurrence proven by biopsy.
- 6.2 The following are not acceptable as evidence of progression:
  - 6.21 Ascites with negative cytology for tumor cells.
  - 6.22 Pleural effusion with negative cytology.
  - 6.23 Computerized Axial Tomography (CAT), MRI, or liver scan findings alone on a single determination.
  - 6.24 Bone scan alone.
  - 6.25 Barium enema findings alone.
  - 6.26 "Blumer" shelf.

## 7.0 STUDY PARAMETERS

### 7.1 Before Randomization

#### All Patients:

- Rev. 6/94 a) CXR must be done  $\leq$  2 weeks prior to resection or randomization.  
 Rev. 8/99 b) All initial lab values must be done  $\leq$  2 weeks prior to randomization.  
 c) If white blood cell count (WBC) & platelet count are abnormal, they must be repeated within 48 hours prior to randomization.  
 d) CT scan or MRI is suggested, but optional.

**NOTE:** When documenting initial results on the ECOG Flow Sheet, please clearly record the actual date on which the scan/test was done. Do NOT use the date of Day 1 of protocol treatment unless the scan/test was actually done that day.

Rev. 8/99 All follow-up WBC and platelet counts should be done  $<$  48 hours prior to the day of treatment.

|                                                                              | Initial | 1 Month Post-Op | Year 1
(Dukes' B2, B3, C) | Year 2
(Dukes' B2, B3, C) | Year 3, 4
(Dukes' B2, B3, C) | Year 5 & After
(Dukes' B2, B3, C) |
|------------------------------------------------------------------------------|---------|-----------------|------------------------------|------------------------------|---------------------------------|--------------------------------------|
| Eval. for Surgical Complications                                             |         | X               |                              |                              |                                 |                                      |
| History & Physical Examination                                               | X       | X               | q 3 mo                       | q 3 mo                       | q 6 mo                          | q 12 mo                              |
| Height & Weight                                                              | X       | X               | q 3 mo                       | q 3 mo                       | q 6 mo                          | q 12 mo                              |
| ECOG Performance Status                                                      | X       | X               | q 3 mo                       | q 3 mo                       | q 6 mo                          | q 12 mo                              |
| WBC & Platelet Count                                             | X       | X               | q 3 mo                       | q 6 mo                       | q 12 mo                         | q 12 mo                              |
| Creatinine & Bilirubin                                                       | X       | X               | q 3 mo                       | q 6 mo                       | q 12 mo                         | q 12 mo                              |
| CEA                                                              | X       | X               | q 3 mo                       | q 3 mo                       | q 6 mo                          | q 12 mo                              |
| Chest X-Ray                                                                  | X       |                 | q 6 mo                       | q 6 mo                       | q 12 mo                         | q 12 mo                              |
| Colonoscopy or Barium Enema                                      | X       |                 | q 12 mo                      | q 12 mo                      | q 24 mo                         | q 3-5 yrs                |
| Pregnancy Test                                                   | X       |                 |                              |                              |                                 |                                      |
| Submission of Slides & Paraffin-  Embedded Tumor & Normal Tissue |         | X               |                              |                              |                                 |                                      |

 Should be done Day 2 and Day 5 after surgery for patients receiving perioperative chemotherapy.

 Optional.

 Should be done  $\leq$  4 weeks prior to randomization/resection.

 For female patients of childbearing potential who will be receiving chemotherapy.

 MUST be submitted for ECOG patients within 1 month of surgery (see Section 10.0 for details). CALGB patients registering to E3293 must submit only 1 paraffin block from primary tumor.

 It is recommended that patients receive a Colonoscopy or Barium Enema every 3-5 years.

### 7.2 After Pathologic Staging:

#### Dukes' B3 and C Patients Only:

- Rev. 8/99 a) WBC, platelet count, creatinine, and bilirubin should be done  $\leq$  1 week prior to beginning adjuvant chemotherapy (5-FU/leucovorin).  
 Rev. 9/97  
 Rev. 8/99 b) WBC and platelet count should be done weekly while patients are receiving adjuvant chemotherapy

E1292  
SWOG 9250  
CALGB 9395  
NSABP CI63  
ACOSOG E1292  
EPP E1292  
INT 0136  
**REVISED**

Revised 8/99, Addendum #8  
Revised 12/08, Addendum #9

Rev. 9/97, 8/99

(5-FU/leucovorin). At completion of chemotherapy, the schedule above for WBC and platelet count should be followed.

## **8.0 DRUG FORMULATION AND PROCUREMENT**

### **8.1 5-Fluorouracil** (Fluorouracil, 5-FU, Aduvex, Efudex)

#### **8.11 Classification and Description**

Classification: Antimetabolite

Description: 5-FU is a commercially available injection. It is colorless to faint yellow, with a pH of 9.2 (adjusted with sodium hydroxide).

#### **8.12 Mode of Action**

Fluorouracil is a pyrimidine antagonist that interferes with nucleic acid biosynthesis. The deoxyribonucleotide of the drug inhibits thymidylate synthetase, thus inhibiting the formation of thymidylic acid from deoxyuridylic acid, thus interfering in the synthesis of DNA. It also interferes with RNA synthesis.

#### **8.13 Storage and Stability**

Stable for prolonged periods of time at room temperature if protected from light. Inspect for precipitate; if apparent, agitate vial vigorously or gently heat to not greater than 140° F in a water bath. Do not allow to freeze.

#### **8.14 Dose Specifics**

See Section 5.2 regarding specifics of dose delivery for this protocol.

#### **8.15 Administration**

The drug may be given IV push, IV continuous infusion, arterial infusion, intracavitary, intraperitoneally, topically, or orally mixed in water, grape juice, carbonated beverage.

See Section 5.2 for specifics of administration in this protocol.

#### **8.16 Incompatibilities**

Incompatible with Doxorubicin and other anthracyclines.

#### **8.17 Availability**

Commercially available in 500 mg/10 ml ampules and vials, and 1 gm/20 ml, 2.5 gm/50 ml, and 5 gm/100 ml vials.

#### **8.18 Side Effects**

1. Hematologic: Leukopenia, thrombocytopenia, anemia.
2. Dermatologic: Dermatitis, nail changes, hyperpigmentation, hand-foot syndrome with protracted infusions, alopecia. Exposure to strong sunlight may intensify skin reactions to the drug.

3. Gastrointestinal: Nausea, vomiting, anorexia; diarrhea; stomatitis, mucositis, more common with 5-day infusion, occasionally dose-limiting.
4. Neurologic: Cerebellar syndrome (headache and cerebellar ataxia), disorientation, confusion, euphoria, ataxia, and nystagmus.
5. Cardiac: Angina, noted with continuous infusion.
6. Ophthalmic: Eye irritation, nasal discharge, watering of eyes, blurred vision, and photophobia.
7. Other: Weakness and malaise.

#### 8.19 Patient Care Implications

1. Monitor blood counts.
2. Administer antiemetics as indicated.
3. Monitor for diarrhea. Encourage fluids and treat symptomatically.
4. Assess for stomatitis - oral care recommendations as indicated.
5. Monitor for neurologic symptoms (headache, ataxia).
6. Patients on continuous infusions may need instruction regarding central IV catheters and portable IV or IA infusion devices.
7. Inform patient of potential alopecia.

### 8.2 Leucovorin Calcium

#### 8.21 Other Names

Leucovorin, Wellcovorin, citrovorum factor, folinic acid, 5-formyl tetrahydrofolate, LV, LCV.

#### 8.22 Classification

Tetrahydrofolic acid derivative.

8.23 Mode of Action

Leucovorin acts as a biochemical cofactor for 1-carbon transfer reactions in the synthesis of purines and pyrimidines. Leucovorin does not require the enzyme dihydrofolate reductase (DHFR) for conversion to tetrahydrofolic acid. The effects of methotrexate and other DHFR-antagonists are inhibited by leucovorin.

Leucovorin can potentiate the cytotoxic effects of fluorinated pyrimidines (i.e., fluorouracil and floxuridine). After 5-FU is activated within the cell, it is accompanied by a folate cofactor, and inhibits the enzyme thymidylate synthetase, thus inhibiting pyrimidine synthesis. Leucovorin increases the folate pool, thereby increasing the binding of folate cofactor and active 5-FU with thymidylate synthetase.

8.24 Storage and Stability

All dosage forms are stored at room temperature. The reconstituted parenteral solution, 10 mg/ml, is stable for at least 7 days at room temperature. At concentrations of 0.5-0.9 mg/ml the drug is chemically stable for at least 24 hours at room temperature under normal laboratory light. The oral solution, 1 mg/ml, is stable for 14 days refrigerated and 7 days at room temperature.

8.25 Dose Specifics

Leucovorin will be given at a dose of 20 mg/m^2 IV push, days 1-5. Doses should be based on actual weight (estimated dry weight if patient has edema). A cycle of therapy consists of 5 consecutive days of chemotherapy. The full course of adjuvant therapy will consist of 6 cycles.

Cycles will be repeated at the end of 4 weeks (day 29), 8 weeks (day 57), and then every 4 weeks for a total of 6 cycles.

8.26 Preparation

The 50 and 100 mg vials for injection are reconstituted with 5 and 10 ml of sterile water or bacteriostatic water, respectively, resulting in a 10 mg/ml solution. The 350 mg vial is reconstituted with 17 ml of sterile water resulting in a 20 mg/ml solution. The 60 mg bottle for oral solution is reconstituted with 60 ml of aromatic elixir provided, resulting in a 1 mg/ml oral solution.

8.27 Administration

IV push.

8.28 Compatibilities

Leucovorin (0.5-0.9 mg/ml) is chemically stable for at least 24 hours in normal saline, 5% dextrose, 10% dextrose, Ringer's injection or lactated Ringer's injection. Leucovorin (0.03, 0.24 and 0.96 mg/ml) is stable for 48 hours at room and refrigeration temperatures when admixed with floxuridine (FUDR, 1, 2 and 4 mg/ml) in normal saline. Leucovorin is also compatible with fluorouracil.

**9.0 STATISTICAL CONSIDERATIONS**

The primary objective of this study is to compare 6 months of adjuvant therapy with 5-FU and leucovorin to the same adjuvant therapy enhanced with perioperative therapy with continuous infusion 5-FU in Dukes' B3 and C patients with regard to the disease free interval and survival. This study is designed to be able to detect a clinically meaningful improvement in survival with 82% power while maintaining an overall significance level of 5% in a one-sided test, assuming patients are followed for 3 years after closure of the study to accrual. If 5 years of follow-up time were available, the power will be 91%. For Dukes' C patients, a clinically meaningful improvement in survival was taken to be an improvement in 5-year survival from 55% to 65%. For Dukes' B3 patients, this is an improvement in 5-year rates from 75% to 81%. To estimate the required sample sizes we assume exponential survival and a group sequential designed with an O'Brien-Fleming upper bound for early rejection of the null hypothesis of no treatment difference.

Assuming a 5-year survival rate of 75% for Dukes' B3 patients and 55% for Dukes' C patients in the adjuvant therapy alone arm, this study will require 800 analyzable patients (400 in each arm) to obtain the stated power using a stratified logrank test. Calculations assume that approximately 70% of the Dukes' B3 and C patients will be Dukes' C and 30% will be Dukes' B3. Since pathological staging is determined only after randomization, the accrual goal needs to be expressed in terms of Dukes' A,

B, C, and D patients. Using data on staging\* it is projected that 40% of all patients will be Dukes' B3 or C thus requiring a total accrual goal of 2000 patients to obtain the required number of B3 and C patients. As these projections are very approximate, accrual will be closely monitored during the first year and the accrual goals will be revised as necessary. For Dukes' A, B1, B2, and D patients, there will be no formal treatment comparisons. However, these patients will be followed to gather more information about disease progression and survival.

Perioperative therapy will require the full participation of the group's surgeons and will be feasible only in member institutions. Thus, this study will not benefit from referrals from outside institutions, which normally comprise 60-75% of the patient population in adjuvant trials. Assuming that the annual rate will be 750 - 875 total patients/year (300-350 B3 and C patients / year), < 25% of the current accrual rate to intergroup study E2288, this study will need about 2-3 years to complete accrual.

We will assume that the patients will be followed for 3 years after the closure of the study to accrual and that 3 interim analyses will be conducted at 2.5 years (1/2 year before the end of accrual), 3.5 years, and 5 years. If the study is not terminated at the end of 5 years, a final analysis will be conducted at 6 years (3 years of follow-up after closure to accrual). The critical values corresponding to these times will be 3.3358, 2.4524, 1.8978, and 1.7480 corresponding to nominal significance levels of .0004, .007, .03, and .04. The chosen interim analysis times closely approximate equal increments in the total number of expected deaths (25%, 50%, and 75% respectively).

\* DeVita, Vincent T., Hellman, Samuel, & Rosenberg, Steven A. (1985). *Cancer: Principles & Practice of Oncology*, (Vol. 1, 2nd ed.). Philadelphia: J.B. Lippincott Company.

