In 1996, an interim analysis demonstrated no significant differences in the disease-free survival or overall survival for any of the arms. This was reported at the ASCO meeting in May, 1996 (12). Because there were no differences in outcome and because the duration

Rev. 9/97 of the treatment for all the leucovorin arms was 6 months vs. the 12 months length of the 5-FU/Levamisole arm, the 5-FU/low dose leucovorin arm has emerged as the obvious choice for treating patients in the community. Further close analysis and follow-up of greater than 4 years has held up these findings (13).

Rev. 9/97 The study proposed in this concept combines the perioperative approach with the now standard adjuvant chemotherapy for colon cancer, 5-FU and leucovorin. Since all the previous studies mentioned have shown a benefit for Dukes' C patients, all Dukes' C patients will receive the 5-FU/leucovorin. The proper treatment for Dukes' B patients is not as clear since many studies did not show a statistically significant benefit for this group. Because of these data, the Dukes' B2 patients will be randomized for the perioperative part of this study only. They will not receive the post-operative 5-FU/leucovorin.

Rev. 9/97 For the B3 patients, although no study has proven a benefit for adjuvant chemotherapy, it is also true that the studies have not been large enough to look specifically at the subgroup.

Because of the poorer survival of this group it is felt they should be treated in the same fashion as the C patients and be eligible for both stages of the protocol.

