### 2.0 **OBJECTIVES**

Rev. 9/97 2.1 To determine if adjuvant therapy with one week of continuous 5-FU given within 24 hours of a curative colon resection followed by 6 months of 5-FU/leucovorin is effective in prolonging the disease free interval and increasing survival in patients with Dukes' B3 or C colon cancer, when compared to patients who are treated with 5-FU/leucovorin only. Endpoints include: treatment failure--as defined by recurrence of local/regional or distant metastases--and survival.

Rev. 9/97 2.2 To determine if a week of perioperative continuous 5-FU affects disease-free survival and survival in patients with Dukes' B2 colon cancer.

2.3 To establish within ECOG a Central Tissue Repository for paraffin blocks and a frozen tissue bank.

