#### 5.13 Pathologic Findings which Prevent Further Chemotherapy

Upon receipt of the final surgical pathology report from the contributing institution's pathology department, Dukes' A, B1, and D patients will have perioperative 5-FU **discontinued**, if so assigned, and will receive NO further adjuvant treatment. These patients will be treated at the discretion of their physician and survival data will continue to be collected on these patients until the time of death. Dukes' B2 patients will have perioperative 5-FU **continued** to completion, if so assigned, but will receive NO further adjuvant treatment. These patients will be followed on observation until relapse or death.

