### 5.2 Chemotherapy Guidelines

#### 5.21 Perioperative 5-FU

Patients randomized to the perioperative 5-FU arm must begin treatment within 24 hours of the completion of the curative resection. They will receive 600 mg/m^2/day of 5-FU as a continuous IV infusion over 24 hours for 7 days. Doses of 5-FU should be based on actual weight. See Section 5.41.

Upon receipt of the final surgical pathology report from the contributing institution's pathology department, Dukes' A, B1, and D patient should have perioperative 5-FU chemotherapy **discontinued**. Dukes' B2, B3, and C patients should have perioperative 5-FU **continued** to completion.

Rev. 9/97

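### Objective 2.2 promises to determine the effect of perioperative 5-FU in Dukes' B2, but Section 9.0 rules out a formal B2 comparison, so the objective has no planned inferential analysis

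*Protocol*

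**What the plan says.** **Objective.** Protocol Section 2.0, item 2.2 (marked as revised 9/97): "To determine if a week of perioperative continuous 5-FU affects disease-free survival and survival in patients with Dukes' B2 colon cancer".

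**Analysis.** Protocol Section 9.0 names the B3/C comparison as primary and sizes only that one. Of the remaining stages it says "For Dukes' A, B1, B2, and D patients, there will be no formal treatment comparisons", and then "However, these patients will be followed to gather more information about disease progression and survival".

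**How B2 patients are handled elsewhere in the Protocol.**
- Section 1.1: "the Dukes' B2 patients will be randomized for the perioperative part of this study only".
- Section 5.21: "Dukes' B2, B3, and C patients should have perioperative 5-FU continued to completion". In A, B1 and D the infusion is stopped once the pathology report arrives.
- Section 5.13, on B2: "These patients will be followed on observation until relapse or death".
- Schema and Section 3: B2, B3 and C are re-registered. A, B1 and D go off study and only their survival is collected.
- Section 7.1: the yearly follow-up columns are headed B2, B3 and C together.

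**The concern.** To determine whether a treatment affects an outcome, one has to compare the randomized arms inferentially. Objective 2.2 asks for that in B2, and Section 9.0 says it will not be done. An analysis plan written under this Protocol must depart from one of the two sections. If it adds a B2 test, it contradicts Section 9.0. If it omits one, objective 2.2 goes unanswered.

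B2 patients complete the randomized infusion, receive no protocol chemotherapy afterwards and are followed for recurrence. They can therefore show the effect of the perioperative week without later 5-FU/leucovorin. Unless the sections are reconciled, any B2 result reported later, favourable or null, can be called unplanned despite being a numbered objective.

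**Working it through.** **1. Is a B2 comparison planned anywhere?** Section 9.0 plans a stratified logrank test for B3 and C only. Section 1.34 plans logrank tests and interaction models by gender and by racial/ethnic group, not by Dukes' stage. So subgroups that are not objectives have named tests, while the B2 objective has none. The B2 objective and the exclusion sentence both stand in the body of the Protocol, so the conflict does not come from the amendment log.

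**2. The plan's own figure, which covers B3/C only.** Inputs from Section 9.0:
- 800 patients, 400 per arm, 70% C and 30% B3.
- 5-year survival 55% to 65% in C and 75% to 81% in B3.
- Exponential survival, with "maintaining an overall significance level of 5% in a one-sided test".
- Accrual of 3 years (the look at 2.5 years is half a year before accrual ends), with the final analysis at 6 years.

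Formulas:
- Hazard λ = −ln(S5)/5, and HR = ln(S5 treated)/ln(S5 control). C: ln 0.65/ln 0.55 = 0.721. B3: ln 0.81/ln 0.75 = 0.732.
- Probability of death with uniform accrual over A years and F further years: p = 1 − [exp(−λF) − exp(−λ(A+F))]/(λA).
- Power = Φ(√(D/4)·|ln HR| − 1.645).

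Results with A = 3:
- F = 3. C: 280 × (0.413 + 0.319) = 205 deaths. B3: 120 × (0.227 + 0.172) = 48 deaths. Total 253, average HR 0.723. Power = Φ(2.58 − 1.645) = 82.6% for a fixed sample, and 81.4% when simulated with the stated critical values. The Protocol says "able to detect a clinically meaningful improvement in survival with 82% power".
- F = 5. 336 deaths. Power = Φ(2.975 − 1.645) = 90.8%, against the stated 91%.

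The primary figures reproduce, and none of them uses B2 patients.

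**3. What a B2 comparison could deliver.** The Protocol gives no B2 share, B2 control survival or B2 target effect, so all three are assumptions:
- Share 20% to 40% of the 2000 accrued, or 400 to 800 patients. B3/C takes 800, which leaves 1200 for A, B1, B2 and D together.
- 5-year control survival 70% to 85%.
- HR 0.72, borrowed from the Dukes' C target.

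Deaths D = (n/2)(p control + p treated), with A = 3:

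| B2 patients | 5-year control survival | F (years) | Deaths | One-sided 5% power |
|---|---|---|---|---|
| 400 | 85% | 3 | 200 × (0.136 + 0.100) ≈ 47 | Φ(1.127 − 1.645) = 30% |
| 800 | 70% | 3 | 400 × (0.273 + 0.206) ≈ 192 | Φ(2.273 − 1.645) ≈ 74% |
| 400 | 85% | 5 | 200 × (0.190 + 0.141) ≈ 66 | Φ(1.337 − 1.645) = 38% |
| 800 | 70% | 5 | 400 × (0.370 + 0.283) ≈ 261 | Φ(2.654 − 1.645) = 84% |

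About 245 deaths would be needed for 82% power at this hazard ratio. Only the most favourable corner, with 5 years of follow-up, gets there.

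**4. Precision.** The two-sided 95% interval around an observed HR of 0.72 is 0.72 × exp(±1.96 × 2/√D). With about 47 deaths it runs from 0.41 to 1.27, and with about 192 deaths from 0.54 to 0.96.

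**The case against.** The best defence is that Section 9.0 excludes only *formal* comparisons. It names one primary objective, B3/C, and declining a test in a stage that was never sized is a respectable choice. The figures above partly support it, since power is below 82% over most of the assumed range. This stands as a reason to keep any B2 analysis secondary. It does not remove the conflict: the Protocol does not give low power as its reason, and objective 2.2 still says determine.

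A reader might infer more than the documents support:
- *That the B2 question cannot be answered.* This is true of the formal plan but not of the data. B2 patients are randomized and followed for relapse and death, so curves and an effect estimate by arm remain possible.
- *That B2 is the only followed stage without later protocol chemotherapy.* Dukes' A and B1 are also followed for survival and receive none. B2 differs because it completes the infusion and is followed for recurrence.
- *That a stage-by-treatment test across B2, B3 and C is needed.* No objective asks for it. B3 and C patients receive 5-FU/leucovorin in both arms and B2 patients receive none, so an interaction would mix stage with background chemotherapy.
- *That B2 is certainly underpowered.* That depends on assumptions. At the favourable end with 5 years of follow-up, power is about 84%.

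**Conclusion.** The contradiction is real. Objective 2.2 has no planned inferential analysis, because Section 9.0 expressly excludes one. It should be fixed, but it is not critical: it concerns a non-primary objective and leaves the B3/C sample size, power, alpha and critical values unchanged.

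Its size can only be given as a range. Under the stated assumptions a B2 survival comparison would have about 47 to 192 deaths and 30% to 74% power at year 6, or 66 to 261 deaths and 38% to 84% at year 8. These powers are one-sided at 5%, to match the primary test. Objective 2.2 says affects, which has no direction, and a two-sided 5% test would have less: about 20% to 62% at year 6. That argues for estimation with an interval rather than a confirmatory test.

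**What to change.** **Preferred.** In Section 9.0, remove B2 from the sentence that excludes formal comparisons. Add a secondary analysis for objective 2.2 in all randomized B2 patients by assigned arm: hazard ratio with two-sided 95% confidence interval and a logrank test, for survival and for disease-free survival. Label it as not sized, outside the primary alpha and not confirmatory. State the expected number of B2 deaths and the precision they give, with the assumptions behind them. Do not add a stage-by-treatment test.

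**Alternative.** Reword objective 2.2 as descriptive. This reconciles the text but gives up the randomized B2 comparison.

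**Cost.** A few sentences. The B2 follow-up is already scheduled, so there are no new data and no change to the sample size or primary alpha. The downsides of the preferred change are two extra secondary tests and having to state openly that B2 precision is limited.

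### Section 9.0: the interim looks fall at about 27, 50 and 81% of expected deaths, not 25, 50 and 75%, and the printed critical values are not a 5% O'Brien-Fleming bound at 25/50/75%; the effect on type I error is minor

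*Protocol*

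**What the plan says.** All of this is in Protocol Section 9.0.

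- Error rate: the design detects the target survival difference, "while maintaining an overall significance level of 5% in a one-sided test". The bound is called O'Brien-Fleming, with no variant or spending function named.
- Timing: "3 interim analyses will be conducted at 2.5 years (1/2 year before the end of accrual), 3.5 years, and 5 years". The final analysis is at 6 years, three years after accrual closes, so these times imply 3-year accrual.
- Thresholds: "The critical values corresponding to these times will be 3.3358, 2.4524, 1.8978, and 1.7480", with nominal levels .0004, .007, .03 and .04.
- Information fractions: "The chosen interim analysis times closely approximate equal increments in the total number of expected deaths (25%, 50%, and 75% respectively").
- Planning inputs: exponential survival; 800 analyzable Dukes' B3 and C patients, 400 per arm; 70% C and 30% B3; 5-year survival of 55% against 65% in C and 75% against 81% in B3. Accrual is put at about 2-3 years, at 300-350 B3 and C patients a year.

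**The concern.** The critical values are the trial's rules for declaring efficacy. An O'Brien-Fleming bound depends on the fraction of final deaths available at each look. The section therefore gives two descriptions of the same design, calendar times and percentages of deaths, and both should lead to the printed values.

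If they disagree, a monitoring committee cannot tell whether the third look is due at year 5 or at 75% of deaths. Nor can a reader recompute the bound, because its form is not named. The question is whether the mismatch is real and whether it threatens the 5% level.

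**Working it through.** **1. The figures that do reproduce.** The upper normal tail areas of the four printed values are .00043, .0071, .0289 and .0402, which round to the stated nominal levels. The stated power is also close. With d the expected deaths per stratum at 6 years, the drift is √Σ d(ln HR)²/4, with hazard ratios .721 (C) and .732 (B3). This is √(205.1 × .1074/4 + 47.9 × .0969/4) ≈ 2.58. With the printed bound it gives 81.5% power, against 82% stated. At 8 years (336 deaths) it gives 90.1%, against 91% stated. The inputs and the 3-year accrual reading are therefore sound.

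**2. Expected deaths at the look times.** The hazards are λ = −ln(S₅)/5: C .1196 and .0862, B3 .0575 and .0421 (control and experimental). With uniform accrual over A years, no dropout and a = min(t, A), the probability that a planned patient has died by time t is

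p(t) = [a − (e^(−λ(t−a)) − e^(−λt))/λ]/A.

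For A = 3:

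- Year 5: p = .3384, .2583 (C) and .1814, .1366 (B3). Deaths = 280 × (.3384 + .2583) + 120 × (.1814 + .1366) = 205.2.
- Year 6: p = .4130, .3195 (C) and .2272, .1722 (B3). Deaths = 280 × .7325 + 120 × .3994 = 253.0.
- Ratio: 205.2/253.0 = 81.1%.

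| | 2.5 y | 3.5 y | 5 y | 6 y |
|---|---|---|---|---|
| Deaths, alternative | 67.0 | 124.6 | 205.2 | 253.0 |
| % of 6-year deaths | 26.5 | 49.2 | 81.1 | 100 |
| Deaths, null | 77.0 | 142.6 | 233.0 | 285.8 |
| % of 6-year deaths | 26.9 | 49.9 | 81.5 | 100 |

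Solving the same formula for 75% gives about 4.7 years, not 5. Faster accrual moves the third look further from 75%: for accrual of 800/350 = 2.29 to 3 years it lies between 81 and 83%.

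**3. What an O'Brien-Fleming bound would be.** The classic form is c = C/√t, with C set so that the overall one-sided error is 5%. At quarters C = 1.7331, so the third value is 1.7331/√.75 = 2.001. The Lan-DeMets form spends 2 − 2Φ(1.96/√t) by fraction t.

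| Bound | Look 1 | Look 2 | Look 3 | Final |
|---|---|---|---|---|
| Printed | 3.3358 | 2.4524 | 1.8978 | 1.7480 |
| Classic, 25/50/75% | 3.466 | 2.451 | 2.001 | 1.733 |
| Lan-DeMets, 25/50/75% | 3.750 | 2.540 | 2.016 | 1.720 |
| Classic, look times (null to alternative) | 3.35-3.38 | 2.46-2.48 | 1.93 | 1.74 |
| Lan-DeMets, look times (null to alternative) | 3.60-3.63 | 2.54-2.56 | 1.91 | 1.74 |

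The printed third value is more than 0.10 below either form at 75%. Its nominal level is .029, against .023 for the classic form.

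**4. Overall error of the printed values.** This is the probability that any look crosses its value, with correlation √(tⱼ/tₖ) between looks, by recursive integration.

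| Look fractions | One-sided error |
|---|---|
| Exactly 25/50/75/100% | 5.21% (5.22% by simulation) |
| Planned times, 3-year accrual | 5.04% (null), 5.06% (alternative) |
| Same times, 2.67-year accrual (800/300) | 4.99%, 5.01% |
| Same times, 2.29-year accrual (800/350) | 4.94%, 4.96% |

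**The case against.** The strongest defence is that the section ties the critical values to the calendar times and gives the percentages separately, as an approximation. At those times the error is 5.04-5.06%, which is 5% at the precision the protocol uses. The classic bound at the look-time fractions has nominal levels that round to .0004, .007, .03 and .04, exactly as printed, and its values lie within about 0.04 of the printed ones. Accrual is given only as a range, and the small excess changes sign within it.

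This defence stands on the size of the effect. It does not rescue the text. Calling 27% and 49-50% close to 25% and 50% is fair, but 81% is not close to 75%. The printed third value is wrong for the fraction that the section attaches to it.

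A reader might also infer three stronger things, which the documents do not support:

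- **That the late third look pushes the error above 5%.** The reverse is true: moving that look from 75% to about 81% brings the error down from 5.21% to about 5.05%.
- **That the first look is too easy at the planned times.** This depends on comparing it with 25%, or with Lan-DeMets spending, which the protocol does not name. The classic value at the look times is 3.35-3.38, against 3.3358 printed.
- **That the origin of the values is known.** Lan-DeMets spending at about 31/53/83% gives 3.336, 2.452, 1.898 and 1.745, near what 2.5-year accrual would produce. No text says so, the final value still differs, and no variant tried matches all four exactly.

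**Conclusion.** The point holds as an internal inconsistency of minor severity. The stated information fraction for the year-5 look is wrong (about 81%, not 75%). The printed critical values are not a one-sided 5% O'Brien-Fleming bound at 25/50/75%, and they match neither form exactly at the planned times.

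The cost in type I error is 0.21 percentage points if the looks are triggered at exactly 25/50/75% of deaths. At the calendar times it is at most 0.06 points. It would be an overstatement to say that the planned design fails to hold 5%.

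These figures assume exponential survival, uniform accrual, the 70/30 stage mix, no dropout, and final information equal to the deaths at 6 years. The finding on the third look holds for any accrual from 2.29 to 3 years.

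**What to change.** In Section 9.0, replace the three percentages with about 27%, 49-50% and 81%, and state which form of the O'Brien-Fleming bound is used. Print the matching values: about 3.35-3.38, 2.46-2.48, 1.93 and 1.74 for the classic form, or about 3.60-3.63, 2.54-2.56, 1.91 and 1.74 for Lan-DeMets. Either choice fits the present wording. State also that the values will be recomputed at the death fractions observed at each look, since accrual is given only as a range.

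If the looks are meant to occur at 25, 50 and 75% of deaths, print 3.466, 2.451, 2.001 and 1.733 for the classic form and correct the calendar times; the third look then falls at about 4.7 years under 3-year accrual.

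The cost is one recalculated line, with no added patients or data. The year-5 threshold becomes slightly stricter and the final one very slightly easier. With Lan-DeMets, the first two looks also become somewhat stricter.
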